### Blinding

2.8

Due to the nature of the intervention, both investigators and participants cannot be blinded. However, because a standardized smartphone application is provided, the threat of bias due to investigator blinding failure may be low.

### Assessment

2.9

Assessments are scheduled at baseline (T1), post-intervention (fourth week; T2), and follow-up (eighth week; T3). The assessment will be performed as a self-report assessment. If participants drop out, they will not be assessed further. Table 2 summarizes the assessment time points.

**Table 2 tab2:** Study assessment points.

	Screening	T1	T2	T3
Demographic information	○			
MBI-GS		○	○	○
UWES		○	○	○
PSS		○	○	○
CAMS-R		○	○	○
IVS		○	○	○

T1, baseline; T2, post-intervention; T3, follow-up; MBI-GS, Maslach burnout inventory—general survey; UWES, The Utrecht work engagement scale; PSS, Perceived stress scale; CAMS-R, Cognitive and affective mindfulness scale—revised; IVS, integrative vitality scale.

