### Discontinuation criteria

2.5

The discontinuation criteria for this study will include the following:

When a participant repeatedly complains of psychological or physical discomfort and wishes to drop out of the study.When a participant wishes to drop out for other reasons.

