### Sample size

2.6

The minimum sample size was calculated using the G* Power program (35). A value of 0.15 indicating a small effect size and a significance level of 0.05 were set, and the power was applied as 0.80. The calculation indicated that a minimum of 90 participants is required, with a minimum of 45 participants per group. Considering a dropout rate of 20%, a maximum of 57 participants per group and a total of 114 participants will be recruited.

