### Statistical analyses

2.13

Analyses will be conducted according to the Intention-To-Treat (ITT) principle, and missing data will be imputed using the expectation maximization algorithm.

First, to investigate the effectiveness of MMT, a 2 (group: experimental vs. control) × 2 (survey time: T1 vs. T2) repeated-measures ANOVA will be performed for MBI-GS, UWES, PSS, CMAS-R, and IVS. If the interaction between the group and survey time is significant, a simple main effect analysis will be performed. Second, a paired *t-*test will be performed on MBI-GS, UWES, PSS, CMAS-R, and IVS in the experimental group to examine the follow-up effect of MMT. Third, a subgroup analysis will be performed to investigate the difference in effectiveness depending on the amount of application usage. For this purpose, 2 (subgroup: high-usage vs. low-usage) × 2 (survey time: baseline vs. post-intervention) repeated-measures ANOVA will be performed. Data from both the experimental and control groups will be used for subgroup analysis. If the interaction between the subgroup and survey time is significant, a simple main effect analysis will be performed. Fourth, a mediating effect analysis will be performed to investigate whether mindfulness and subjective vitality mediate the relationship between application use and burnout or work engagement.

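### Assessment ends for everyone who drops out, so avoidable gaps in self-report outcomes are left to imputation in an analysis labelled intention-to-treat

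*Protocol article*

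**What the plan says.** Four sections of the protocol article bear on this.

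- **2.9 Assessment** sets the data-collection rule: "If participants drop out, they will not be assessed further". It has no exception.
- **2.5 Discontinuation criteria** gives two ways to leave: "When a participant repeatedly complains of psychological or physical discomfort and wishes to drop out of the study", and "When a participant wishes to drop out for other reasons". It offers no route by which someone ends the training but goes on answering questionnaires.
- **2.13 Statistical analyses** states: "Analyses will be conducted according to the Intention-To-Treat (ITT) principle, and missing data will be imputed using the expectation maximization algorithm".
- **2.6 Sample size** sets the expected loss: "Considering a dropout rate of 20%, a maximum of 57 participants per group and a total of 114 participants will be recruited".

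All outcomes are self-report scales (2.9 to 2.11). Controls have no app during the first 4 weeks (2.4.2), and the main comparison is group by time from T1 to T2 (2.13).

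**The concern.** Intention-to-treat analysis works best when the outcome is sought from everyone randomised, whether or not they keep to the intervention. Here the protocol itself switches off collection for anyone who drops out and hands the gap to EM. An analysis plan written later cannot recover scores that were never requested.

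EM rests on the missingness being explained by what was observed. A person who leaves before T2 has baseline scores and demographic data, and perhaps some app usage up to that point. Discomfort or lack of benefit during the training would not show in the baseline scores, yet discomfort is one of the leaving reasons that the protocol names. Before T2, leaving because of the app can happen only in the experimental arm, so the two arms may lose different kinds of people. At stake is the trust one can place in the T1–T2 group comparison, on which the primary objective depends.

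**Working it through.** **1. The plan's own figures.** Section 2.6 gives: "A value of 0.15 indicating a small effect size and a significance level of 0.05 were set, and the power was applied as 0.80". I read 0.15 as Cohen's f for the within-between interaction (2 groups, m = 2 times). The correlation ρ between times is not given; I assume 0.5.

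- λ = f² × N × m / (1 − ρ) = 0.0225 × 90 × 2 / 0.5 = 8.1, with 1 and 88 degrees of freedom. Power is 0.804; at N = 88 it is 0.795. This reproduces the plan: "The calculation indicated that a minimum of 90 participants is required, with a minimum of 45 participants per group". With ρ = 0.3 or 0.7 the required N would be 126 or 56.
- Dropout allowance: 45 / (1 − 0.20) = 56.25, rounded up to 57 per group, or 114 in total. This also reproduces.

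The sample size is not in dispute here.

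**2. How many values could be imputed.** 114 − 90 = 24 people, or 12 of 57 per arm (21%). Section 2.6 does not say whether the 20% is reached by T2 or over all 8 weeks, so at the planned rate about 24 is the upper figure for T2.

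**3. Whether those scores could be collected.** The five scales have 15 (MBI-GS), 9 (UWES), 10 (PSS), 10 (CAMS-R) and 22 (IVS) items, 66 in all. All are self-reported and none needs the app or a clinic visit.

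**4. What the gap could do (illustration; all inputs except the 20% are assumed).** With f = 0.15 as read above, the difference in change between arms is 4f = 0.60 SD, taken here as the gain of stayers over controls. Let d be the dropout proportion in an arm and s the amount by which dropouts' true change is worse than that of stayers in the same arm. If imputation gives dropouts the course of stayers in their own arm:

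bias = d(exp) × s(exp) − d(con) × s(con)

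| Scenario at 20% dropout per arm | True effect | Estimate | Bias |
|---|---|---|---|
| Only experimental dropouts worse, s = 0.30 | 0.54 | 0.60 | +0.06 |
| Only experimental dropouts worse, s = 0.60 | 0.48 | 0.60 | +0.12 |
| Dropouts equally worse in both arms | 0.60 | 0.60 | 0 |
| Only control dropouts worse, s = 0.30 | 0.66 | 0.60 | −0.06 |

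If EM were run on both arms pooled with no group term, dropouts in each arm would on average receive the midpoint, 0.30. The estimate would be (0.8 × 0.60 + 0.2 × 0.30) − (0.2 × 0.30) = 0.48. That is 0.12 too low if dropouts truly followed their own arm, and unbiased if experimental dropouts gained nothing.

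**5. Effect of collecting the scores.** No larger sample is needed. With all 114 assessed, the formula in step 1 gives power 0.89, against 0.80 with 90, provided the effect is the same in everyone. If the effect is diluted in those who stop, power is lower than 0.89.

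**The case against.** The best reply is that section 2.9 covers people who leave the study, not people who stop using the app. The first criterion in 2.5 speaks of leaving the study, and nothing makes low use or non-use a ground for discontinuation. The third objective and 2.13 compare high- and low-usage subgroups at post-intervention, so low users apparently stay in and are assessed. A reader might infer from 2.9 that anyone who stops the app loses T2 and T3; the documents do not say that. This part of the objection stands and narrows the point to those who ask to leave. For them, the protocol still does not ask whether ending participation in the training also means refusing further questionnaires. Those who do refuse cannot be assessed, and the fix exempts them.

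A second reply is that keeping everyone in the arm to which they were randomised and imputing what is missing is a common way to carry out intention-to-treat. That is correct. A reader might take 2.9 and 2.13 to contradict each other, but they do not. The weakness is that the missing data are avoidable.

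A third reply is that the imputation model is not given in the article and that controls may drop out too. This also stands. Such detail may properly sit in an analysis plan, and step 4 shows that it decides the sign of any bias.

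**Conclusion.** The point holds as a weakness of design. The protocol has a categorical rule that creates missing outcomes which could often be collected, and its only remedy is an imputation whose key assumption is doubtful for people who leave during training. About 24 of 114 participants could be affected at the planned dropout.

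A reader might go further and conclude that the trial will overstate the effect, for instance by 25% (0.60 against 0.48). The documents do not support that. The 0.60 SD is derived from f = 0.15 and is not stated in the protocol. The 25% also needs zero gain in every experimental dropout, imputation within arm, 20% dropout already by T2 and no bias in controls. Under those conditions, with the experimental dropouts' gain between half and none, the bias is 0.06 to 0.12 SD. Under others it is zero or negative. Size and direction are therefore undetermined, and collecting the scores is the direct way to find out.

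**What to change.** Replace the sentence in section 2.9 with: *Participants who stop the intervention will still be sent the T2 and T3 questionnaires unless they withdraw consent to further data collection.* In addition:

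- record stopping the intervention and withdrawal from assessment as separate events, each with date and reason;
- analyse all observed scores in the arm to which the person was randomised;
- reserve imputation for what is still missing.

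This alters data collection only and leaves the criteria for discontinuation as they are. The cost is a change to the protocol and consent wording, some extra self-report forms, and a few reminders to people who stopped. According to section 3.1 recruitment has not begun, so the change can still apply to every participant, and the sample size stays as it is.

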### Primary outcomes

2.10

#### Maslach burnout inventory—general survey (MBI-GS)

2.10.1

The Korean version of the MBI-GS will be used to assess burnout (36). This scale consists of 5 items for burnout, 4 items for cynicism, and 6 items for decreased job efficacy. Decreased job efficacy is reverse scored. The MBI-GS is a self-reported 5-point Likert scale. Each item ranges from 1 to 5. The total score ranges from 15 to 75. A higher score indicates more severe burnout. In a previous study (36), Cronbach’s alpha was 0.90 for burnout, 0.81 for cynicism, and 0.86 for decreased job efficacy.

#### The Utrecht work engagement scale (UWES)

2.10.2

The Korean version of the UWES will be used to assess work engagement (37). This scale consists of 3 items for vigor, 3 items for dedication, and 3 items for absorption. The UWES scale is a self-reported 7-point Likert scale. Each item ranges from 0 to 6. The total score ranges from 0 to 54. A higher score indicates more immersion in one’s job. In previous studies (37), Cronbach’s alpha was 0.91 for vigor, 0.89 for dedication, and 0.90 for absorption.

### Secondary outcomes

2.11

#### Perceived stress scale (PSS)

2.11.1

The Korean version of the PSS will be used to assess perceived stress (38). This scale consists of 5 items for negative perception and 5 items for positive perception. Positive perception is reverse scored. The PSS is a self-reported 5-point Likert scale. Each item ranges from 1 to 5. The total score ranges from 10 to 50. A higher score indicates more perceived stress. In a previous study (38), Cronbach’s alpha was 0.77 for negative perception and 0.74 for positive perception.

#### Cognitive and affective mindfulness scale-revised (CAMS-R)

2.11.2

The Korean version of CAMS-R will be used to assess mindfulness (39). This scale consists of 4 items for awareness, 4 items for attention, and 2 items for acceptance. CAMS-R is a self-reported 4-point Likert scale. Each item ranges from 1 to 4, and one item from the attention subfactor is reverse-scored. The total score ranges from 10 to 40. A higher score indicates a higher level of mindfulness. In a previous study (39), Cronbach’s alpha was 0.70 overall, 0.58 for awareness, 0.73 for attention, and 0.35 for acceptance.

#### Integrative vitality scale (IVS)

2.11.3

The IVS is a self-report scale that measures physical and psychological vitality (40). The scale consists of 22 items, 11 items for physical vitality and 11 items for psychological vitality. The IVS is a self-report 5-point Likert scale. The total score ranges from 0 to 44 for physical vitality and from 0 to 44 for psychological vitality. One item (e.g., My head feels heavy and achy) is reverse scored. Higher scores indicate higher physical and psychological vitality. In a survey of 348 people, Cronbach’s alpha was 0.91 for physical vitality, 0.91 for psychological vitality, and 0.94 overall (40).

### Data management

2.12

All collected data will be stored on the investigator’s computer and encrypted. Personal information will be replaced with a unique identifier and stored together with research information for 3 years and destroyed thereafter.

### Statistical analyses

2.13

Analyses will be conducted according to the Intention-To-Treat (ITT) principle, and missing data will be imputed using the expectation maximization algorithm.

First, to investigate the effectiveness of MMT, a 2 (group: experimental vs. control) × 2 (survey time: T1 vs. T2) repeated-measures ANOVA will be performed for MBI-GS, UWES, PSS, CMAS-R, and IVS. If the interaction between the group and survey time is significant, a simple main effect analysis will be performed. Second, a paired *t-*test will be performed on MBI-GS, UWES, PSS, CMAS-R, and IVS in the experimental group to examine the follow-up effect of MMT. Third, a subgroup analysis will be performed to investigate the difference in effectiveness depending on the amount of application usage. For this purpose, 2 (subgroup: high-usage vs. low-usage) × 2 (survey time: baseline vs. post-intervention) repeated-measures ANOVA will be performed. Data from both the experimental and control groups will be used for subgroup analysis. If the interaction between the subgroup and survey time is significant, a simple main effect analysis will be performed. Fourth, a mediating effect analysis will be performed to investigate whether mindfulness and subjective vitality mediate the relationship between application use and burnout or work engagement.

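### EM-imputed outcomes are tested as if observed: with arm in the imputation model the primary test rejects too often, and without it the treatment effect is diluted

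*Protocol article*

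**What the plan says.** Section 2.13 of the protocol article opens with two commitments: "Analyses will be conducted according to the Intention-To-Treat (ITT) principle", and "missing data will be imputed using the expectation maximization algorithm". Dropouts therefore stay in the analysis with imputed values.

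The tests named next all need complete data. For effectiveness, a "2 (group: experimental vs. control) × 2 (survey time: T1 vs. T2) repeated-measures ANOVA will be performed" on each of the five scales. For follow-up, a paired t-test "in the experimental group to examine the follow-up effect of MMT". A usage-subgroup ANOVA and a mediation analysis come after these and fall under the same imputation sentence. The section mentions no multiple imputation, combining rule or variance correction, and does not say whether arm enters the imputation model.

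Section 2.6 sets the scale of the problem. 45 per group are needed; after an allowance ("Considering a dropout rate of 20" per cent) 57 per group are recruited, 114 in total. Section 2.9 adds that dropouts have no later assessments. Because all five scales share the same visits (Table 2), someone lost before T2 has no T2 value on any of them.

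**The concern.** The EM algorithm gives sound maximum-likelihood estimates of means and covariances. Used to fill in data, it replaces each missing value by its conditional expectation. An ordinary ANOVA or t-test on the completed dataset then makes two mistakes. The filled values lie on the regression line and carry no residual scatter, so the variance is understated. They are also counted as independent observations, so the degrees of freedom are those of 114 people when fewer were measured. Section 2.6 treats dropouts as contributing nothing to power; section 2.13 then analyses them as fully observed.

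The imputation model decides which harm follows. If it contains arm, the estimate is unbiased but its standard error is too small. If it omits arm, dropouts from both arms are filled towards a common mean and the difference between arms shrinks. At stake are the tests of both primary outcomes, burnout and work engagement, and of the follow-up objective.

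**Working it through.** **Inputs from the document.** 57 per arm, 1:1 allocation, 20% dropout, alpha 0.05, power 0.80, effect size 0.15 (read as Cohen's f), minimum N of 90. **Assumed:** T1–T2 correlation r of 0.3 to 0.7, T1 complete, T2 missing completely at random in a fraction d, unit variances, one completed dataset, and T1 (with or without arm) as the only predictor of T2.

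**Step 1: reproduce the planned sample size.** For the 2 × 2 interaction, λ = f² × N × m / (1 − r), with m = 2 visits and 1 and N − 2 degrees of freedom. At r = 0.5, λ = 0.0225 × 90 × 2 / 0.5 = 8.1, and power is 0.804. The required N is 178 at r = 0, 126 at r = 0.3 and 56 at r = 0.7, so the stated 90 implies r of about 0.5. Dropout: 45 / 0.8 = 56.25, rounded up to 57; 2 × 57 = 114. The plan's figures reproduce.

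**Step 2: closed form, imputation within arm.** The interaction test equals a two-sample t-test on the change score. Per-person variance of the change:

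- reported by the test: (1 − d) × 2(1 − r) + d × (1 − r)²
- true: (1 − r)² + (1 − r²) / (1 − d)

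At r = 0.5 and d = 0.2:

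- reported: 0.8 × 1 + 0.2 × 0.25 = 0.85, so SE = √(2 × 0.85 / 57) = 0.173
- true: 0.25 + 0.75 / 0.8 = 1.1875, so SE = √(2 × 1.1875 / 57) = 0.204
- ratio √(0.85 / 1.1875) = 0.846; the two-sided type I error is the normal tail beyond ±1.96 × 0.846, which is 9.7%

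**Step 3: simulation under the null** (57 per arm, 40,000 trials per cell).

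| r | T2 missing | Arm in model: closed form | Arm in model: simulated | Arm in model: paired t | Arm omitted: interaction | Arm omitted: paired t |
|---|---|---|---|---|---|---|
| 0.3 | 20% | 9.0% | 9.3% | 9.3% | 5.1% | 7.0% |
| 0.5 | 20% | 9.7% | 10.2% | 9.8% | 5.1% | 7.6% |
| 0.7 | 20% | 10.5% | 10.4% | 10.6% | 4.9% | 8.0% |
| 0.3 | 10% | 6.7% | 6.8% | 6.4% | 5.1% | 6.0% |
| 0.5 | 10% | 7.0% | 7.1% | 7.2% | 4.9% | 5.8% |
| 0.7 | 10% | 7.3% | 7.4% | 7.3% | 5.1% | 6.2% |

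At 5% missing with arm in the model, the interaction test rejects in 5.9–6.0%. Entering arm as a covariate, in place of separate models by arm, gives 8.8–10.6% at 20% missing (fewer runs). Adding a random residual to a single fill-in still gives 8.7–9.0% at r = 0.3 to 0.5.

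**Step 4: bias when arm is omitted.** A fraction d of each arm is filled from the common mean, so the expected difference is (1 − d) × δ = 0.8 × 0.60 = 0.48 SD. Simulation at r = 0.5 gives 0.479. Power for that effect is 0.784, against 0.895 with within-arm imputation, although the latter figure comes from an anti-conservative test.

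**Step 5: is imputation the cause?** The same test on observed pairs only, at 20% missing, rejects in about 4.9% at all three correlations, with reported SE 0.99–1.00 of the true SE. A likelihood analysis of the observed data adjusted for T1 also held about 5%, with no bias.

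**The case against.** The strongest case against is that the size of the problem depends on things the article does not state.

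- **Arm in the imputation model.** The list of variables is a detail commonly left to an analysis plan. That is fair, and the omission alone is not the point. The point is that the method as stated fails with either choice.
- **20% at T2.** Section 2.6 gives 20% as a recruitment allowance and ties it to no visit. If it is the eight-week figure, less is missing at T2, where the primary comparison is made. This stands, which is why the 10% and 5% results are reported alongside.
- **One completed dataset.** The article does not say single or once. It does say that values are imputed, and it follows this with tests that need completed data and no combining step, so a single dataset is the natural reading. It remains an inference.
- **Better predictors.** Auxiliary variables would reduce the inflation. The scope is limited for the primary comparison, since a person lost before T2 has no T2 scale at all and baseline data are the main predictors left. For T3 there is more scope, because T2 is known for those who drop out later.

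A reader might infer that the 5% error rate simply doubles at the planned dropout. The document does not support that unconditionally: it needs arm in the model, a single fill-in and 20% missing already at T2. Nor is every p-value too small: with arm omitted, the primary test is close to nominal. The article names no confidence intervals, so none can be called wrong.

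**Conclusion.** The concern holds in conditional form. The imputation method and the complete-data tests are both stated, and together they give wrong inference under either choice of imputation model. With arm included, the primary test rejects a true null in about 9–10.5% of trials at 20% missing and about 7% at 10%. With arm omitted, the primary test holds its level, but the effect is diluted by roughly the missing fraction and the within-arm follow-up test rejects in 7–8% at 20% missing. As the choice is open, it could be made after the data are seen.

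The direction is certain given a single fill-in. The size is less so: it rests on missingness completely at random, complete T1, correlations of 0.3 to 0.7 and no auxiliary predictors. The paired-test figures come from a two-visit layout and serve as a guide for T1 against T3.

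**What to change.** For the T1–T2 comparison and the T1–T3 follow-up, replace EM imputation plus ANOVA or t-test with a likelihood-based repeated-measures model on all observed data from randomised participants. Include arm by time and an unstructured covariance, with T1 either as a covariate or constrained equal across arms. The group contrast at T2 then serves the primary objective and the T1–T3 contrast within the experimental arm serves the follow-up.

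Alternatively, keep the planned tests and use multiple imputation done separately by arm, combined by Rubin's rules. For the usage-subgroup and mediation analyses, likewise use multiple imputation or a likelihood method in place of EM fill-in.

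Cost: somewhat more analysis work in standard software, and an amendment to the named primary analysis. The article reports that recruitment has not started, so no data are affected. For the planned change-score comparison, honest standard errors will exceed the understated ones (0.204 against 0.173 in the worked case). Adjusting for T1 wins part of this back: √(2 × 0.75 / (57 × 0.8)) = 0.181 at the same correlation and missing fraction.

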Mindfulness is a unique attentional ability developed through meditation practice, characterized by present-moment focus and nonjudgmental attitude. Mindfulness training is used to alleviate emotional problems and improve the quality of life in a variety of clinical groups. Previous studies have shown that mindfulness reduces stress, depression, and anxiety, and improves wellbeing (17–22). Furthermore, mindfulness training can improve workers’ mental health and job performance. According to previous studies, mindfulness reduces workers’ stress and burnout (23–26) and improves work engagement and job performance (27–29).

Because of these benefits, mindfulness has recently become a core component of several smartphone-based healthcare applications, such as Headspace and Calm. Previous studies have shown that mobile mindfulness training (MMT) reduces users’ stress, depression, and anxiety, and improves their quality of life (16, 30–33). However, most studies on the effects of mobile mindfulness training have been conducted on students or the general public, with relatively few studies targeting workers (16). Moreover, according to previous research (34), more than half of digital mindfulness-based intervention studies have been conducted with healthcare workers, while less than one-fifth of the studies have been conducted with office workers. Therefore, this study will investigate the effects of MMT on office workers’ stress, burnout, and work engagement.

This study aims to verify the effectiveness of MMT on the mental health of office workers and explore its mechanisms. The primary objective of this study is to investigate whether a four-week MMT improves office workers’ mental health, stress, burnout, and work engagement. The results of this study are predicted as follows: (i) The experimental group will exhibit reduced burnout compared to the control group after 4 weeks. (ii) The experimental group will exhibit enhanced work engagement compared to the control group after 4 weeks. (iii) The experimental group will exhibit lower perceived stress compared to the control group after 4 weeks. (iv) The experimental group will exhibit increased mindfulness compared to the control group after 4 weeks. (v) The experimental group will exhibit superior subjective vitality compared to the control group after 4 weeks.

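### The effectiveness test is a change-score comparison; adjusting the T2 score for the T1 score already collected would estimate the same effect more precisely

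*Protocol article*

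**What the plan says.** The primary objective in the Introduction reads "The primary objective of this study is to investigate whether a four-week MMT improves office workers’ mental health, stress, burnout, and work engagement", and the hypotheses under it are differences between the arms after 4 weeks. The first analysis in section 2.13 serves that objective: "a 2 (group: experimental vs. control) × 2 (survey time: T1 vs. T2) repeated-measures ANOVA will be performed" for MBI-GS, UWES, PSS, CAMS-R and IVS. The interaction is the deciding term: "If the interaction between the group and survey time is significant, a simple main effect analysis will be performed". The article mentions no baseline-adjusted model.

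Section 2.6 bases the sample size on these statements: "A value of 0.15 indicating a small effect size and a significance level of 0.05 were set"; "the power was applied as 0.80"; "a minimum of 90 participants is required, with a minimum of 45 participants per group". It then adds the allowance for dropout: "Considering a dropout rate of 20%, a maximum of 57 participants per group and a total of 114 participants will be recruited". It names neither the metric of the 0.15 nor a correlation between repeated measurements.

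Sections 2.1 and 2.9 (Table 2) have every outcome measured at T1 and T2 in both arms. Section 2.7 sets 1:1 random allocation.

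**The concern.** The group-by-time interaction subtracts the whole baseline score from the T2 score, however weakly the two are correlated. When r is below 1, that removes too much and carries baseline noise into the comparison. ANCOVA subtracts only the part of the baseline that predicts T2, and it adjusts for chance imbalance at T1.

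At stake is precision on both primary outcomes, MBI-GS and UWES, and on the three secondary scales. The trial is sized for 80% power, so the choice of model affects the chance of missing an effect of the planned size. It also decides how far that chance depends on a correlation that the article does not give.

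**Working it through.** **Inputs.** From section 2.6: effect size 0.15, alpha 0.05, power 0.80, 90 evaluable (45 per arm), 20% dropout, 114 recruited. From section 2.7: 1:1 allocation. Assumptions, not stated in the article: 0.15 is Cohen's f; r = 0.5 as the base case, varied from 0 to 0.9; equal SDs at T1 and T2; complete data.

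**1. Reproduce the plan's figure.** For a within-between interaction with m = 2 times, the noncentrality is λ = N f² m/(1−r) = 90 × 0.0225 × 2/0.5 = 8.1, on 1 and 88 df. Power is 0.804, and 90 is the smallest even N that reaches 0.80. Dropout: 45/(1−0.20) = 56.25, rounded up to 57 per arm, 114 in total. Of the variants tried, no other gives 90: r = 0.3 gives 126, r = 0.7 gives 56, three times with r = 0.5 gives 74, and a between-subjects factor with r = 0.5 gives 264 (two times) or 236 (three times). So f = 0.15 with r = 0.5 is a plausible reading, but it is an inference.

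**2. Convert to a mean difference.** In a 2 × 2 interaction each cell departs by f SDs, so the between-arm difference in change is 4f = 4 × 0.15 = 0.60 SD.

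**3. Check the equivalence.** The t-test on change has noncentrality d√N/(2√V), with V = 2(1−r) = 1 at r = 0.5. This is 0.60 × 9.487/2 = 2.846, and 2.846² = 8.1, the same as λ in step 1. The two tests are one.

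**4. Compare variances.** In units of σ², change score: 2(1−r). ANCOVA: 1−r². Ratio: (1−r)(1+r)/[2(1−r)] = (1+r)/2. At r = 0.5 this is 0.75, and the SE ratio is √0.75 = 0.866, about 13% smaller.

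**5. Power for ANCOVA.** One further df is charged (N−3), and the variance is multiplied by 1 + 1/(N−4) for chance baseline imbalance. At N = 90 and r = 0.5: 0.75 × (1 + 1/86) = 0.759, and the noncentrality is 0.60 × 9.487/(2 × 0.871) = 3.27, giving power 0.898.

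| r | Variance ratio | Power, N = 90: change / ANCOVA | Power, N = 114: change / ANCOVA | N for 80%: change / ANCOVA |
|---|---|---|---|---|
| 0 | 0.50 | 0.512 / 0.799 | 0.612 / 0.885 | 178 / 92 |
| 0.3 | 0.65 | 0.662 / 0.835 | 0.765 / 0.912 | 126 / 84 |
| 0.4 | 0.70 | 0.729 / 0.863 | 0.826 / 0.932 | 108 / 78 |
| 0.5 | 0.75 | 0.804 / 0.898 | 0.888 / 0.954 | 90 / 70 |
| 0.6 | 0.80 | 0.882 / 0.938 | 0.944 / 0.977 | 72 / 60 |
| 0.7 | 0.85 | 0.953 / 0.975 | 0.984 / 0.993 | 56 / 48 |
| 0.8 | 0.90 | 0.994 / 0.997 | 0.999 / 1.000 | 38 / 36 |
| 0.9 | 0.95 | 1.000 / 1.000 | 1.000 / 1.000 | 20 / 20 |

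The N = 114 columns treat all recruited participants as observed. They are an upper bound, because imputing missing scores adds no information.

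**6. Simulation check** (20,000 trials, 45 per arm, r = 0.5). Type I error is 0.050 for both tests. Power is 0.800 for the change score and 0.897 for ANCOVA. Both estimators average 0.599 against a true 0.60, with empirical SEs of 0.211 and 0.184.

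**The case against.** The strongest reply is that nothing is broken. The planned test is unbiased in a randomised trial, keeps its alpha, and matches the sample-size calculation: on the inputs that reproduce 90, it has the 80% power claimed. That stands. A reader might infer that the test is invalid or that the trial misses its own power target; the documents and the simulation support neither.

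The second reply is that the size of the gain rests on inferred inputs. That also stands. Neither 0.60 SD nor r = 0.5 appears in the article, and if these scales correlate at 0.8 or above over four weeks, the gain hardly matters. If all 114 were observed, the gain at r = 0.5 would be about 7 points (0.888 to 0.954), against about 9 at N = 90. What the reply does not remove is the direction: under the equal-SD assumption the ratio (1+r)/2 is below 1 for every r below 1.

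A reader might also infer that the simple main effects after a significant interaction are meant as proof of efficacy from within-arm change. The article does not say so. The step depends on the between-arm interaction being significant, and simple effects in a 2 × 2 design can include the comparison of the arms at T2, which is randomised. The article does not say which will be run, so this is no ground for criticism.

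**Conclusion.** The point holds as a loss of efficiency, not of validity. The article settles on a change-score test although the data for a more precise estimate of the same effect will be in hand. On the reading that reproduces 90, the chance of missing a 0.60 SD effect at 45 per arm falls from about 20% to about 10%, or the completers needed for 80% power fall from 90 to about 70. The benefit is largest where the plan is most exposed: if r is 0.3 to 0.4, the planned test has power of 0.66 to 0.73 at N = 90, against 0.84 to 0.86 with adjustment. Near r = 0.7 the gain is about two points, and from 0.8 it is negligible.

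These figures rest on f = 0.15, equal SDs, complete data and 1:1 allocation. The correlation is unknown and governs the size of the gain.

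**What to change.** In section 2.13, replace the 2 × 2 ANOVA for MBI-GS and UWES, and likewise for PSS, CAMS-R and IVS, with an ANCOVA of the T2 score on arm adjusted for the T1 score, or an equivalent baseline-adjusted mixed model. Base the efficacy conclusion on the adjusted between-arm difference. In section 2.6, name the effect-size metric and the assumed T1–T2 correlation, so that the basis of the 90 can be read.

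The cost is one degree of freedom, a small variance term for chance imbalance (already counted above) and a changed analysis sentence. No assessment, instrument or recruitment target changes. Section 3.1 states that recruitment has not begun, so the change can be made before any data exist.
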